### Patient and public involvement

The RISE intervention was developed in cocreation with relevant end-users and stakeholders: people with stroke and their relatives, physiotherapists, (inter)national behavioural and movement behaviour experts, hardware and software developers and technical experts. The co-creation was an iterative process in which the behaviour change wheel for developing behaviour change interventions was followed step-by-step.^19^ The RISE eCoaching system was developed based on the CeHRes road map for designing eHealth technologies.^53^,^53^ Feedback from pilot study interviews with physiotherapists, participants and their PS was directly incorporated into the RISE trial. Design sketches of the RISE eCoaching system were critically reviewed by people with stroke and their relatives. During the current RISE trial, participants and physiotherapists will be interviewed as part of the evaluation and implementation. A panel of experienced experts will be consulted biannually for advice regarding study procedures.^54^

## Ethics and dissemination

The RISE intervention study has been approved by the Medical Ethics Review Committee Utrecht NedMec NL83940.000.23 (Clinicaltrials.gov registration NCT06124248). Study amendments will be notified to the pertinent ethics committee. Informed consent (online supplemental file 1) will be obtained by researchers. Only the study staff will have access to the final dataset containing pseudonymised data. There are no declarations of interest. As soon as all data have been collected and analysed, pseudonymised data will be shared on reasonable request. Findings will be disseminated through international peer-reviewed journals and conferences. End results will be shared with participants and involved parties. Julius Clinical Utrecht is involved as Data Monitoring Committee. All (serious) adverse events related to the intervention or higher will be registered via line listing and sent to the Medical Ethics Review Committee Utrecht NedMec within three months after the end of the study.

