### Control group (usual care)

There will be no restrictions for receiving other care as usual. Participants in the experimental and control group receive usual care according to national stroke guidelines.^18^ At T1–T4, participants are asked about all of their healthcare utilisation via the institute for Medical Technology Assessment (iMTA) Medical Consumption Questionnaire (iMCQ) (^22^).

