### Primary outcome

The effect of the RISE intervention on the number of MACE will be measured based on the 2000 Consensus Conference of the European College of Cardiology and American College of Cardiology criteria.^23^ MACE is a composite of clinical end points of recurrent stroke or TIA, acute coronary events and cardiovascular death.^3^ Stroke recurrence will be diagnosed by acute neurological symptoms and signs and confirmed by MRI. TIAs are defined according to American Heart Association guidelines.^24^ Acute coronary events (myocardial infarction (MI), cardiac revascularisation and hospitalisation with unstable angina) are diagnosed according to the 2000 Consensus Conference of the European College of Cardiology and American College of Cardiology criteria.^23^ Deaths are regarded to be attributable to a cardiovascular cause (fatal MI, fatal stroke (ie, death within 1 month of MI or stroke), sudden death caused by definite coronary artery disease and congestive heart failure) unless a non-cardiac death could be confirmed. Recurrence of MACE will be collected via medical records of the GP. In the Netherlands, where this study takes place, all hospital-based care—including diagnoses, admissions and clinical events—is systematically reported back to the participants’ GP. Additionally, participants are asked in a questionnaire if any MACE occurred. In case of any discrepancy between the GP’s medical record and questionnaire, the researchers will contact the GP to obtain the correct information from the medical professionals involved. Data from the GP’s medical record will remain the primary source of data collection.

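### Adverse events are registered only if related to the intervention, so harms other than MACE cannot be compared between the randomised arms from that listing

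*Protocol article*

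**What the plan says.** The protocol article has one statement on adverse events, under Ethics and dissemination: "All (serious) adverse events related to the intervention or higher will be registered via line listing". The listing is then "sent to the Medical Ethics Review Committee Utrecht NedMec within three months after the end of the study". No relatedness scale is given, so *or higher* has nothing to refer to.

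For the comparator, the section on the control group says: "Participants in the experimental and control group receive usual care according to national stroke guidelines". Only the experimental arm receives RISE in addition. The same section says that at T1–T4 "participants are asked about all of their healthcare utilisation".

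Cardiovascular events follow a different route. Under Primary outcome, "MACE is a composite of clinical end points of recurrent stroke or TIA, acute coronary events and cardiovascular death", and "Recurrence of MACE will be collected via medical records of the GP", with a participant questionnaire as a cross-check. The Statistical analysis section compares MACE between arms with a Cox model.

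**The concern.** Filtering on relatedness before registration turns a randomised comparison into a one-arm list. A control participant who falls and breaks a hip is not entered. An experimental participant with the same injury is entered only if someone attributes it to RISE. Falls, injuries and admissions occur after stroke with or without coaching, so case-by-case attribution cannot show whether RISE adds to them. The comparison with controls can.

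This matters here because the intervention asks people within six months of a first stroke to sit less and move more, largely at home. The protocol recognises a safety question: it excludes people whose comorbidities make that change unsafe. It also presents the trial as a foundation for implementation in standard care, and that decision needs evidence on harms outside the primary endpoint.

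**Working it through.** **1. Which harms are compared between arms?**

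| Harm | Collected in both arms? | By-arm comparison described? |
|---|---|---|
| Recurrent stroke or TIA, acute coronary events, cardiovascular death | Yes: GP records and questionnaire (Primary outcome) | Yes: Cox model (Statistical analysis) |
| Confirmed non-cardiac death | Identified when deaths are classified (Primary outcome) | No |
| Other admissions | Indirectly, as healthcare use at T1–T4 (Table 3) | Only as costs (Secondary outcomes) |
| Falls, fractures, musculoskeletal injury | No such outcome in Table 3; listed only if related to RISE | No |

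The gap is in the last three rows.

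**2. What can the filtered listing show?** Let N be the number followed per arm, p the background risk of a non-MACE event, d the true excess under RISE, and r the share of experimental-arm events judged related.

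- Expected listing, experimental arm: N × (p + d) × r
- Expected listing, control arm: essentially 0

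The quantity of interest is d, but the listing gives only the product (p + d) × r. For N, take 376 per arm and 20% loss to follow-up (Sample size section): 376 × 0.80 = 300.8, about 301. Two illustrations with assumed values:

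- No excess: p = 0.10, d = 0, r = 0.20 gives 301 × 0.10 × 0.20 = 6.0 against 0.
- Five-point excess: p = 0.10, d = 0.05, r = 2/15 gives 301 × 0.15 × 2/15 = 6.0 against 0.

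The same listing fits both, so it cannot tell them apart.

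**3. What would registration in both arms give?** The 95% half-width for a risk difference at equal risk p is 1.96 × √(2p(1 − p)/301). The document gives no rate for non-MACE serious events, so p is an assumption, shown as a range:

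- p = 0.05: 1.96 × √(0.095/301) = 0.035
- p = 0.10: 1.96 × √(0.18/301) = 0.048
- p = 0.20: 1.96 × √(0.32/301) = 0.064

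**4. The plan's own figure.** The plan gives no number for harms. The only figure used is the arm size. The Lachin–Foulkes formula with event risks of 20% and 13% at one year, 1.5 years of uniform accrual, 2.5 years in total, 20% yearly dropout, two-sided 0.05 and power 0.85 gives 750.6, or 751 against the stated 752. So 376 per arm is taken as it stands.

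**The case against.** The strongest reply is that the trial does compare harms. A reader might infer from the adverse-event sentence that no harm can be compared between arms. The document does not support that. The main serious cardiovascular harms are the primary outcome, ascertained in both arms whatever their cause. Healthcare use and patient-reported outcomes add indirect information. Classifying deaths identifies the non-cardiac ones, and the Abstract's expansion of MACE even reads as if any death counted, although the Primary outcome section limits it to cardiovascular death. This part of the reply stands and confines the point to harms other than MACE.

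A second reply is that the sentence is garbled, may describe only what goes to the ethics committee, and comes from an article that condenses a full protocol not shown. That is possible. But the sentence says which events are registered, not merely which are forwarded. It states a rule rather than leaving one out. If the full protocol registers everything, correcting the sentence costs almost nothing.

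Two further inferences should be resisted:

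- **Monitoring committee.** The article says "Julius Clinical Utrecht is involved as Data Monitoring Committee" and nothing about what that body receives or when. The timing, "within three months after the end of the study", belongs to the ethics committee. That the monitoring committee lacks by-arm safety data cannot be concluded from silence.
- **Unblinded attribution.** Participants and physiotherapists know the allocation, and the T1 assessor does not. The article does not say who judges relatedness, so a judgement made with allocation known is not established.

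**Conclusion.** The point holds for harms other than MACE. Under the rule as written the control arm contributes essentially nothing to the adverse-event listing, so the listing gives no between-arm information on falls, injuries, other admissions or confirmed non-cardiac deaths. No other part of the article sets up that comparison. Cardiovascular harms are compared properly.

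The conclusion rests on the literal wording of one sentence and on controls having no exposure to RISE. It needs no event rate. The half-widths of 3.5 to 6.4 points only indicate what registration in both arms would offer. A reader might want a single power figure for the lost comparison, but the document gives no base rate to support one. The protocol plans on 20% of controls having MACE alone, so a low rate for all serious events would sit badly with its own figures, and any such calculation must allow for the 20% loss. Registration in both arms should be adopted, but the primary analysis is not at risk.

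**What to change.** Replace the sentence under Ethics and dissemination so that:

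- serious adverse events, including injurious falls, are registered identically in both arms at T1–T4, regardless of relatedness;
- the sources are the GP records and the healthcare-utilisation questionnaire already in use in both arms;
- relatedness is recorded as an attribute of each event, on a stated scale, with *or higher* corrected or defined against it;
- non-MACE serious events are tabulated by arm with a risk difference and 95% confidence interval.

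The listing for the ethics committee can still be drawn from this register as a subset.

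The cost is a small amendment and some extra data extraction and entry. It is not nil: GP records are described only for MACE, and nothing shows that the utilisation questionnaire identifies injurious falls, so an item may have to be added. No new visit is needed.

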## Discussion

This article represents the design of the RISE intervention randomised controlled trial for people with first-ever stroke who require secondary prevention based on their 24-hour movement behaviour. In this study, we will investigate the effectiveness of the RISE blended behaviour intervention in people with a first-ever stroke at risk to prevent major adverse cardiovascular events (ie, recurrent stroke or TIA, acute coronary events and cardiovascular death, MACE). Next to that, the cost-effectiveness of the intervention for MACE prevention and QALYs will be investigated, and changes in 24-hour movement behaviour will be analysed.

In 2017, the WHO launched the programme, Rehabilitation 2030, with a call for action for global rehabilitation needs.^55^ With an increasing number of patients living with the consequences of stroke, the focus in healthcare shifts towards secondary prevention.^15^ Due to this increasing number of patients and the associated costs, healthcare sectors around the world increasingly focus on personalised cost-effective care for people at risk.^4^ The RISE intervention fits within this scope. People at risk receive the intervention at home from a primary care RISE physiotherapist. By means of a personalised focus on healthier 24-hour movement behaviour, we are aiming to prevent the occurrence of MACE in people living with stroke.

A strength of this study is the personalised and behaviour-oriented approach of the RISE intervention. Behaviour is complex, and being physically active is dependent on more factors than solely physical capacities.^19^ Movement behaviour takes place throughout the day and is mainly driven by personal habits and routines. These are directly related to the individual’s social and physical environment.^10^ Based on promising results of our pilot study results regarding PS, participants involve a participatory supporter who joins them in the RISE intervention.^14^ Furthermore, the RISE intervention takes place in the participants’ home, allowing the physiotherapist to take into account all environmental factors related to the 24-hour movement behaviour. Including these societal and environmental elements will contribute to a sustainable movement behavioural change.^56^

Proper training of therapists is essential to minimise deviations from the intended treatment protocol.^57^ Therefore, RISE physiotherapists will be extensively educated during a 4-day course. This is particularly important as the RISE intervention requires a different approach than regular physiotherapy. Current national guidelines are focused on the improvement of disorders, activities and participation within the personal and environmental context, whereas the RISE intervention requires personalised and behaviour-oriented coaching towards sustainable behaviour change.^15^ Therefore, RISE physiotherapists follow an intensive educational programme on personalised coaching, applying behaviour change techniques and motivational interviewing. All RISE physiotherapists become part of the RISE learning community in which adherence to the RISE protocol will be optimised during 3-monthly meetings. Our learning community set-up is based on an effective trial that also showed the importance of proper training and booster sessions.^58^

A limitation of the RISE intervention might be its suitability for people with limited digital literacy skills. Usage of the RISE eCoaching system requires a certain level of digital skills. To overcome this problem as much as possible, the RISE eCoaching system is developed in collaboration with people with stroke to optimise usability of the system. Next to that, RISE physiotherapist coaches participants in the usage of the system during the 15-week intervention period. Another limitation is that the RISE intervention is currently only available in Dutch, and therefore not yet accessible to non-Dutch speakers. Verbal communication is essential for the personalised coaching involved, and due to the practical difficulty of involving physiotherapists fluent in other languages, the choice was made to currently only offer the RISE intervention in Dutch. As a result, non-Dutch speakers were excluded from participation. In future studies, we will explore how to make the intervention accessible to non-Dutch speakers.

A sustainable 24-hour movement behaviour change is needed to gain long-term benefits of lowering cardiovascular events and mortality in patients with stroke. The RISE intervention offers this foundation by integrating behaviour change techniques, the RISE eCoaching system, involvement of PS and extensively trained RISE physiotherapists. Consequently, the RISE intervention is expected to be (cost-)effective compared with usual care, and hence this study will offer a foundation for implementing the RISE intervention in standard poststroke care.
